Therefore, the primary aim of this research study is to investigate the efficacy of a stress management and resiliency training program (SMART-D) in patients with major depressive disorder, with a current moderate episode.

Specific Aims:

1. To compare outcomes of depressive symptoms (PHQ-9 and HAM-D) over 6 months following an eight-week program of SMART-D therapy + treatment as usual versus treatment as usual for patients with major depression with a current moderate episode.

Hypothesis: We hypothesize that the intervention will lead to improved depression outcomes by reducing depressive symptoms after recovery from an acute episode and reduce relapse rates over a 6 month period.

1. To compare measures of resilience (Connor Davidson Resiliency Scale) and perceived stress (Perceived Stress Scale) over 6 months following an eight-week program of SMART-D therapy versus treatment as usual for patients with major depression.

Hypothesis: We also hypothesize that the intervention will be associated with improved resilience and decreased perceived stress as secondary outcomes, which are presumably the agents of change with the SMART-D intervention.

1. To assess the influence of genetic polymorphisms of Serotonin Transporter gene (SLC6A4) and Catechol-O-Methyltransferase gene between early adverse experiences, current burden of stress, depression and treatment response to SMART-D therapy.

Hypothesis: We hypothesize that some genetic variations will be associated with greater depression in participants with adverse childhood experiences and subsequently reduced response to SMART-D intervention.

Scientific Approach:

SMART is a resiliency training program created at the Mayo Clinic (Sood 2013). Key components of SMART include identifying emotional signs of stress and recognizing different thinking modes of the brain, such as the default mode and the focused mode. Participants learn attention training and practice finding novelty, using curiosity and kindness to view the physical world, and the relationships within them. The cognitive aspects of training include intentional practice of principles of gratitude, compassion, acceptance, forgiveness, higher meaning and purpose to interpret and reframe day-to-day life experiences.

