| Connor-Davidson Scale |  | | **X** | **X** | | **X** | **X** | |
| PHQ-9 | **X** | | **X** | **X** | | **X** | **X** | |
| Hamilton Rating Scale | **X** | | **X** | **X** | | **X** | **X** | |
| Cohen Perceived Stress Scale |  | | **X** | **X** | | **X** | **X** | |
| GAD-7 Scale |  | | **X** | **X** | | **X** | **X** | |
|  |  | |  |  | |  |  | |
| LASA- QOL scale |  | | **X** | **X** | | **X** | **X** | |
| Neff’s Self-Compassion Scale |  | | **X** | **X** | | **X** | **X** | |
| Mindful Attention Awareness Scale |  | | **X** | **X** | | **X** | **X** | |
| Current Burden of Stress scale | |  | X |  |  | | |  |
| Adverse Childhood Experiences Questionnaire | |  | X |  |  | | |  |

Randomization and Blinding:

Randomization sequence will be generated using Microsoft Excel 2013 using random block sizes of either three, four, or 5random numbers- depending on how many participants are accrued for one group- by an independent researcher not involved with the study. Allocation sequence will be concealed from the research coordinator assessing participants in sequentially numbered, opaque, sealed and stapled envelopes. Due to the nature of the study design, blinding of participants will not be possible. Outcome assessors will be blind to the group allocation. Study participants will be told not to share their group allocation to the assessors. Statistical analysis will be performed by an independent statistician, who will be blind to the group allocation.

Intervention:

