Outcome measures included measures of depression, perceived stress, resilience and anxiety. Treatment effectiveness will be assessed utilizing the objective ratings of the Hamilton rating scale for depression – 17 item (Hamilton 1960) and self-reported Patient Health Questionaire-9 (Kroenke and Spitzer 2002). The use of two different instruments of depression outcomes comes from a meta-analysis of psychotherapy studies that showed significant differences between clinician-rated and self-report measures of improvement following psychotherapy for depression. This suggests the possibility that different symptoms are suited for subjective or objective ratings (Cuipers 2010). Perceived stress will be measured using the Perceived Stress Scale (PSS), a 10-item self-administered scale that measures the degree to which one’s life is appraised as stressful (Cohen 1983). Anxiety will be measured using the self-reported Generalized Anxiety Questionnaire (Spitzer 2006). Resilience will be assessed by the Connor-Davidson Resilience Scale (CD-RISC) (Connor-Davidson 2003). Internal consistency will be assessed in our sample by measuring omega at baseline and follow-up periods for each group separately. Quality of Life will be measured using a 6 item linear analog self-assessment (LASA), questionnaire. Respondents rate their QOL on a 0–10 numerical analog scale for each domain i.e., mental, emotional, physical, spiritual, social and overall QOL (Singh et al 2014). To measure potential mechanisms of action of SMART therapy, we will measure mindfulness using a 10-item scale, The Mindful Attention Awareness Scale (MAAS), and we will measure self-compassion using a 12-item Self-Compassion Scale- Short form(SCS-SF).

Power Calculation:

Sample size calculation is based on effect sizes obtained from the feasibility study we completed recently. Although we found a within group standardized mean difference >1 for reduction in depressive symptoms in our pilot study, we will assume a moderate standardized mean difference of 0.7 for the RCT, , alpha level =0.05 (two-tailed), power of 80%. Based on these assumptions, we will require a sample of 40 participants in each group providing allowance for 25% drop-out rate to detect statistically significant differences in depressive symptoms between the 2 groups.

Statistical Analysis:

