The SMART-D and TAU groups will be compared on baseline demographic and clinical characteristics. Primary analysis will apply Intention-to-treat analysis to compare treatment outcomes of depression, with participants analyzed based on their initial randomization, at post-SMART-D intervention, at the 3 month and 6 month time post intervention time points. Analysis of the primary outcome (depression) and secondary outcomes (perceived stress, resilience) will be carried out using linear mixed effects regression with results presented as mean differences (and 95% CIs). Secondary analysis will examine the relationship of stress as a predictor of depression and depression as a predictor of stress. For each outcome, a single mixed effects model will be fitted incorporating baseline, post-intervention, 3- and 6-month data using random effects to allow for the repeated measures within an individual, and clustering of individuals within each treatment site. Separate parameters will be estimated for group differences at 3- and 6-months post-intervention; scores at baseline will be added as a covariate. Differences in the outcomes of SMART-D and TAU groups will be assessed using linear mixed models, with individuals clustered within each treatment site and assessment times clustered within individuals. We will run an unadjusted model and compare this to an adjusted model, with the unadjusted model as our primary analysis, to evaluate robustness of these findings. The adjusted model will include the following as covariates: gender, age, education, marital status, medication use (obtained from interview and chart records), number of previous depressive episodes, baseline anxiety (measured by GAD) and severity of recent depressive episode. The participant’s site and individual participant will be modelled as random effects and the remaining variables will be handled as fixed effects. Conditional maximum likelihood will be used to fit the mixed model to account for the missing data. This approach makes an assumption that data are missing at random. Sensitivity analysis in the form of pattern mixture models will be used to explore the departure from this assumption. We will also perform a per-protocol analysis as a supplementary analysis. Significance will be tested at p < .05 for the primary analysis. False Discovery Rate method will be used to make adjustments for Type I error inflation for secondary outcomes.

References

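### No primary depression scale, visit or decision rule is fixed, and Type I error adjustment covers secondary outcomes only

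*Protocol*

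**What the plan says.** All references are to the Protocol.

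- **Specific Aims, Aim 1** gives both scales and a period, not a visit: "To compare outcomes of depressive symptoms (PHQ-9 and HAM-D) over 6 months".
- **Outcome Measures** assesses treatment effectiveness on the clinician-rated HAM-D and the self-reported PHQ-9, and explains why both are kept: "The use of two different instruments of depression outcomes comes from a meta-analysis of psychotherapy studies". The stated reason is that clinician ratings and self-report can give different answers after psychotherapy.
- **Statistical Analysis** names a construct rather than a measure: "Analysis of the primary outcome (depression) and secondary outcomes (perceived stress, resilience) will be carried out using linear mixed effects regression". The primary intention-to-treat comparison is made "at post-SMART-D intervention, at the 3 month and 6 month time post intervention time points". One mixed model is fitted per outcome, and "Separate parameters will be estimated for group differences at 3- and 6-months post-intervention".
- **Statistical Analysis**, on error control: "Significance will be tested at p < .05 for the primary analysis". The next sentence applies the False Discovery Rate method to secondary outcomes.
- **Randomization and Blinding**: participants cannot be blinded, but "Outcome assessors will be blind to the group allocation".

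**The concern.** The protocol recognises Type I error inflation and provides a correction, but the correction stops short of the primary family, where there are already two scales and up to three visits. Nothing says which scale comes first, which visit carries the claim, whether both scales must succeed, or whether the visits are pooled into one test. The choice of which difference to report as the primary result can therefore be made after the data are seen.

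The scales also differ in their protection from bias. PHQ-9 is completed by participants who know their allocation in an open-label trial against usual care, whereas HAM-D is scored by blinded assessors. As written, a single PHQ-9 difference at one visit, with HAM-D showing nothing at any visit, could be presented as a positive primary result.

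**Working it through.** **1. The plan's own figure.** Power Calculation gives a standardized mean difference of 0.7, two-sided alpha 0.05, 80% power, 25% drop-out and 40 per group. The normal formula gives n = 2 × (1.960 + 0.842)² / 0.7² = 2 × 7.849 / 0.49 = 32.04 per group, and 32.04 × 1.25 = 40.05. The stated 40 is reproduced as one comparison at 0.05, with no allowance for a second scale or further visits. (How drop-out is inflated is a separate matter and does not affect this point.)

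**2. How many comparisons.** The text supports three counts:

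- Two: both scales at one contrast.
- Four: both scales at 3 and 6 months, the only visits in the sentence on separate parameters.
- Six: both scales at all three visits listed for the primary comparison.

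**3. Independent tests, as an upper reference.** 1 − 0.95^k gives 9.75% for k = 2, 18.5% for k = 4 and 26.5% for k = 6.

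**4. Correlated tests.** The z-statistics were drawn from a multivariate normal distribution with no treatment effect. The correlation between two comparisons is the between-scale value times the between-visit value where both differ. The entry is the share of draws in which at least one |z| exceeds 1.960. The correlations are assumptions, because the document gives none.

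| Between scales | Between visits | 2 tests | 4 tests | 6 tests |
|---|---|---|---|---|
| 0.5 | 0.4 | 9.1% | 16.6% | 22.9% |
| 0.6 | 0.5 | 8.8% | 15.5% | 21.2% |
| 0.7 | 0.6 | 8.3% | 14.4% | 19.1% |
| 0.8 | 0.7 | 7.8% | 12.8% | 16.5% |

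With stronger correlations (0.9 between scales, 0.8 between visits) the six-test figure is 13.5%.

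**5. A different decision rule.** If both scales had to reach p < .05 at one contrast, the false-positive chance with no effect on either scale would be about 1-2% (0.9% at correlation 0.5, 2.2% at 0.8).

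**6. Power under the possible repairs.** Completers per group: 40 × (1 − 0.25) = 30. The mean of z is 0.7 × √(30/2) = 2.711.

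- One contrast at 0.05: Φ(2.711 − 1.960) = Φ(0.751) = 77.4%. The t-test gives 76.0%.
- One given scale at 0.025, the first Holm step alone: Φ(2.711 − 2.241) = Φ(0.470) = 68.1%. The t-test gives 65.9%.
- Full Holm over two scales, SMD 0.7 on both, between-scale correlation 0.5-0.8, normal approximation: at least one scale succeeds in about 77-83% of trials, and one given scale in about 73%.

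**The case against.** A reader might infer that the protocol sets up six primary tests, each at .05, with a true error rate of 16-23%. The document does not say that. It speaks of one primary analysis and one model per outcome, and its separate-parameter sentence names only 3 and 6 months. It does not say that any single significant result is enough. Under a both-scales rule the error would be below 5%. The 16-23% figure therefore needs three things the text does not supply: the any-one rule, the correlations and a count of six. This objection stands, and it is why the size has to be given by reading.

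It can also be said that a statistical analysis plan, not shown here, may name the contrast and the testing order. Such detail is often left there, and its absence alone would not be a finding. But this protocol does more than stay silent: it defines the primary outcome as an unranked two-scale construct, sets its threshold, and assigns the multiplicity correction to secondary outcomes. That part does not depend on the missing document.

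Finally, Outcome Measures gives a reasoned case for keeping both scales, and HAM-D is not free of expectancy. Its raters are blinded, but the participants answering them know their allocation and are only asked not to reveal it. This stands too. It makes HAM-D a reasonable choice rather than the only one.

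**Conclusion.** The concern holds in a limited form. The protocol fixes a multiplicity rule that leaves its primary family uncorrected, and it fixes no primary scale, visit or decision rule. The error rate of the primary claim is thus undefined, and under a reading the protocol permits it exceeds the nominal 5%. Which row of excess applies depends on the count of comparisons: the smallest, two scales at one contrast, is already above 5% at every correlation examined, and the largest applies only if all three visits are in play. A flat statement that the trial's error rate is 16-23% is not supported. The conclusion that it can exceed 5% does not depend on the particular correlations assumed, but it does depend on any one result being allowed to count.

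**What to change.** Pre-specify one confirmatory contrast before any unblinded analysis: one scale, either at one named visit or averaged over the follow-up visits, which would match the six-month span of Aim 1. Place the other scale and the remaining visits in the existing False Discovery Rate family. HAM-D is a reasonable choice because of its blinded assessors, with the caveat on expectancy above.

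If both scales are to stay co-primary, as the rationale in Outcome Measures suggests, apply Holm across the two at the one named contrast and say that success on either counts.

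The cost is fewer routes to a positive primary result. A single contrast keeps the power of the present calculation, about 76% with 30 completers per group. Holm does not reduce the chance of a positive trial to the 66-68% of its first step: that figure is for one given scale at 0.025, whereas the chance that at least one scale succeeds is at or slightly above the single-contrast figure. The loss falls on any one given scale, at about 73%. No participants, visits or measurements are added. The edit touches Aim 1, Outcome Measures and Statistical Analysis, and any existing analysis plan should be brought into line.
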